## Abstract

**Background:**

Preschoolers’ lifestyles have become physically inactive and sedentary, their eating habits have become unhealthy, and their sleep routines have become increasingly disturbed. Parent-based interventions have shown promise to improve physical activity (PA), improve dietary behavior (DB), and reduce sleep problems among preschoolers. However, because of the recognized obstacles of face-to-face approaches (eg, travel costs and time commitment), easy access and lower costs make eHealth interventions appealing. Previous studies that examined the effectiveness of parent-based eHealth for preschoolers’ PA, DB, and sleep have either emphasized 1 variable or failed to balance PA, DB, and sleep modules and consider the intervention sequence during the intervention period. There is an acknowledged gap in parent-based eHealth interventions that target preschoolers raised in Chinese cultural contexts.

**Objective:**

This study aims to investigate the effectiveness of a parent-based eHealth intervention for PA, DB, and sleep problems among Chinese preschoolers.

**Methods:**

This 2-arm, parallel, randomized controlled trial comprises a 12-week intervention with a 12-week follow-up. A total of 206 parent-child dyads will be randomized to either an eHealth intervention group or a control group. Participants allocated to the eHealth intervention group will receive 12 interactive modules on PA, DB, and sleep, with each module delivered on a weekly basis to reduce the sequence effect on variable outcomes. The intervention is grounded in social cognitive theory. It will be delivered through social media, where parents can obtain valid and updated educational information, have a social rapport, and interact with other group members and facilitators. Participants in the control group will receive weekly brochures on PA, DB, and sleep recommendations from kindergarten teachers, but they will not receive any interactive components. Data will be collected at baseline, 3 months, and 6 months. The primary outcome will be preschoolers’ PA. The secondary outcomes will be preschoolers’ DB, preschoolers’ sleep duration, preschoolers’ sleep problems, parents’ PA, parenting style, and parental feeding style.

**Results:**

Parent-child dyads were recruited in September 2023. Baseline and posttest data collection occurred from October 2023 to March 2024. The follow-up data will be obtained in June 2024. The results of the study are expected to be published in 2025.

**Conclusions:**

The parent-based eHealth intervention has the potential to overcome the barriers of face-to-face interventions and will offer a novel approach for promoting a healthy lifestyle among preschoolers. If this intervention is found to be efficacious, the prevalence of unhealthy lifestyles among preschoolers may be alleviated at a low cost, which not only has a positive influence on the health of individuals and the well-being of the family but also reduces the financial pressure on society to treat diseases caused by poor lifestyle habits.

**Trial Registration:**

ClinicalTrials.gov NCT06025019; https://clinicaltrials.gov/study/NCT06025019

**International Registered Report Identifier (IRRID):**

DERR1-10.2196/58344

## Introduction

### Background

People’s lifestyles affect their health and well-being [1]. The main lifestyle dimensions of physical activity (PA), dietary behavior (DB), and sleep have played pivotal roles in decreasing cardiovascular risk [2], improving brain growth velocity [3], preventing mental disorders [4], improving social interactions [5], and improving the central nervous system [6]. These dimensions appear to be interrelated. PA brings about substantial benefits in not only reducing high-fat calorie consumption [1] but also improving sleep patterns and increasing sleep duration [7]. A longer nighttime sleep duration was shown to be associated with a less frequent intake of fast foods and sugar-sweetened beverages [8], and people with sufficient sleep quality were more likely to form active lifestyles [9]. In the past few decades, individuals’ lifestyles have become physically inactive and sedentary [10], their eating habits have become unhealthy [11], and their sleep routines have become increasingly disturbed [12]. These changes have led to an ever-increasing prevalence of noncommunicable diseases such as diabetes and obesity [13]. Therefore, an effective intervention is needed to reverse this negative trend. A previous study indicated that children of preschool age may respond better to treatment as the lifestyle behaviors in this period are malleable and less entrenched [14]. Lifestyles formed in the early years of life can extend throughout the lifetime and influence lifelong health trajectories [15].

Parents have a profound impact on the healthy lifestyle of preschoolers and are the key agents of behavioral modification [16]. Parents provide an overwhelming majority of cues for PA, diet, and sleep routines and are responsible for role modeling these behaviors among their children [17]. Preschoolers are particularly dependent on their parents since younger children have limited autonomy and rely on parental supervision [18]. A longitudinal study demonstrated that parents’ influence on children’s lifestyle may be attenuated as children age because peer interaction gradually becomes their preferred activity when they grow up [19].

Despite the importance of parental involvement, previous parent-based interventions involving home visits and in-person education have been associated with high attrition rates, with many relying on self-reported assessments, failing to use a randomized controlled study design [20], and showing lower recruitment [21]. Other limitations of delivering interventions face-to-face within the home are related to the associated time commitment for participants [21], the need for childcare for other siblings [22], stigma, parental denial [23], the need to travel [24], and associated costs [23], which have hindered intervention adoption and adherence and have ultimately decreased the effectiveness of these programs. In response, eHealth, which is defined as the cost-effective and secure use of information and communication technologies in support of health, including health care services, health surveillance, health literature, health education, health knowledge, and health research [25], has the potential to address these barriers [26], providing convenience and flexibility for parents and enabling parents to participate regardless of their geographic location [27]. Moreover, personalized information and feedback delivered via eHealth interventions may augment behavioral change strategies [28].

Efficacy trials assessing the effectiveness of parent-based eHealth for preschoolers’ PA, diet, and sleep have been conducted in 12 studies [29-40]. Although these 12 studies demonstrated that participants engaging in eHealth interventions had significant improvements in their healthy lifestyles, 7 studies [29,33,35-38,40] only concentrated on 1 variable, with 2 studies focusing on sleep, 3 focusing on fruit and vegetable intake, and 2 focusing on PA. A study by Ling et al [34] reported that disclosed intervention content between 2 groups may result in insignificant group-by-time changes in PA and diet. The remaining 4 studies [30-32,39] found a significant group-by-time difference in diet, but this effect was not found in PA and sleep. Possible reasons for this may be that these 4 studies involved more diet modules compared to PA and sleep modules. Overall, previous studies that examined the effectiveness of parent-based eHealth on preschoolers’ PA, diet, and sleep have either emphasized 1 variable or failed to balance PA, diet, and sleep modules and consider the intervention sequence during the intervention period. Specifically, more exposure to diet modules relative to fewer PA modules may yield outcomes favoring diet variables. When the posttest was conducted, parent-child dyads may have been more familiar with the modules distributed at the end of the intervention period, thus producing favorable outcomes regarding the content of these modules compared to others.

Empirical relationships obtained in one culture may be a product of its milieu and may not be generalizable to other countries [41]. Very little is currently known about whether parent-based eHealth can effectively improve preschoolers’ PA and diet and reduce sleep problems in China. In the past decade, the prevalence of physical inactivity, unhealthy diet patterns, and sleep problems among Chinese children has increased. Around 70.1% of preschoolers do not meet the PA guidelines recommended by the World Health Organization (WHO) (ie, over 180 minutes of PA daily, including at least 60 minutes of moderate-to-vigorous PA) [42]. The total energy consumption involving fat and sodium exceeds the Chinese Recommended Nutrient Intakes by 10% and 56%, respectively [43]. Over 61% of Chinese preschoolers experienced or are experiencing insufficient sleep and sleep problems (eg, sleep onset latency) [44]. China has the largest population in the world, and the implementation of a traditional face-to-face intervention to improve the unhealthy lifestyles of preschoolers would pose a heavy financial burden on society [44]. An effective and feasible intervention strategy is imperative to tackle these growing health problems.

Currently, the number of smartphone and internet users in China is 1.64 billion and 1028.74 million, respectively [45]. eHealth interventions addressing unhealthy lifestyles could be cost-effective and easily scaled up [46]. Furthermore, affected by Confucianism, Chinese parents emphasize “training” (Guan), which refers to parents’ control and demands [47]. “Guan,” a typical characteristic of Chinese parenting, may generate a profound impact on determining a child’s lifestyle behaviors, including PA, diet, and sleep [48]. Considering the shortcomings revealed in the study design of previous eHealth studies, high-quality robustly designed research studies that balance the intervention content and sequence are needed to determine the effectiveness of eHealth interventions to support behavior change in Chinese preschoolers, with parents being agents of change.

### Research Objective

This study aims to investigate the effectiveness of parent-based eHealth interventions for PA, DB, and sleep among Chinese preschoolers.

## Methods

### Study Design

This study is a 2-arm, parallel, single-blinded, randomized controlled trial designed to promote preschoolers’ PA, DB, and sleep by providing parents with relevant health information through an eHealth modality. The first arm involves an eHealth intervention, which will deliver evidence-based information and interactive components via social media (ie, WeChat, similar to WhatsApp; and TikTok or Douyin, similar to YouTube). The interactive components include push notifications, social rapport, influence agents, goal setting, and personalized feedback. The second arm involves a control intervention, which consists of printed evidence-based educational materials on standard recommendations for PA, diet, and sleep, without interactive components. The primary outcome will be preschoolers’ PA. The secondary outcomes will be preschoolers’ DB, preschoolers’ sleep duration and sleep problems, parents’ PA, parenting style, and parental feeding style. The intervention will last 12 weeks, with a 12-week follow-up. Based on the results of a previous systematic review, the duration of parent-based eHealth interventions varied from 8 weeks to 2 years, with over half of the studies being shorter than 12 weeks [49]. In this case, the 12-week intervention duration, which roughly coincides with the length of a school semester in the Chinese educational system of kindergarten (ie, two 3-month semesters in an academic year), is considered sufficient for behavioral modification. The proposed study design is shown in Figure 1. The study will follow the CONSORT-EHEALTH (Consolidated Standards of Reporting Trials Statement for Randomized Trials: Improving and Standardizing Evaluation Reports of Web-Based and Mobile Health Interventions) guidelines [50].

**Figure 1 figure1:**
[figure not shown]
Study design.

### Ethical Considerations

The study has been approved by the Hong Kong Baptist University Research Ethics Committee (reference number: SOSC-SPEH-2022-23_115). This study has been prospectively registered at the ClinicalTrials.gov Protocol Registration and Results System (PRS) (NCT06025019). Written informed consent will be obtained from all participants or their legal guardians. Personal data (ie, gender, age, and marital status); preschoolers’ PA, diet, and sleep behaviors; and family information (family economic status, parents’ education level, and family structure) will be collected. No other information related to participant identity will be recorded or disclosed. The data collected by the researchers will be destroyed after the project is completed and published (within 7 years). In case of withdrawal, the data will be deleted from the data file immediately. Incentives (honorary certificates) will be offered to families judged to be more active and healthier.

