### Sample Size

A recent systematic review and meta-analysis indicated a small but significant effect size for interventions to improve the PA of children aged younger than 5 years [69]. Interventions that aimed to enhance DB and reduce sleep problems among preschoolers had small to medium effect sizes [9,70]. Based on the information, a priori analysis will be conducted using G*power 3.1.9.6 [71]. A minimum sample size of 82 parent-child dyads in the intervention and control groups separately is required to detect a small effect size (*d*) of 0.3 with a power of 0.80 under the condition of an α level of .05. Considering a 20% potential attrition rate, 206 parent-child dyads in total are needed.

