### Statistical Analysis

All statistical analyses will be conducted using IBM SPSS 27 (IBM Corp), and a 2-sided *P* value <.05 will be considered statistically significant. Baseline characteristics between the intervention group and control group will be compared using the chi-square test for categorical variables and ANOVA for continuous variables. A mixed model, which accounts for missing repeated measures, will be adopted with a 2-level between-group factor (intervention and control) and 2-level within-group factor (postintervention and follow-up assessment) repeated measures analysis of covariance (RM ANCOVA) to examine whether the eHealth-based parenting intervention improves preschoolers’ PA, DB, and sleep compared to the findings in the control group.

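### Deleting all data of every withdrawn dyad discards records that the planned mixed model could use, and biases the comparison if outcome-related withdrawal differs by arm

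*Protocol article*

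**What the plan says.** Three places in the protocol article bear on this.

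- Ethical Considerations: "In case of withdrawal, the data will be deleted from the data file immediately". Nothing confines this to data after withdrawal or to parents who request erasure, and no other section keeps what was collected earlier.
- Statistical Analysis: "A mixed model, which accounts for missing repeated measures, will be adopted". The model compares two arms over two outcome occasions, post-intervention (T2) and follow-up (T3), in a repeated measures analysis of covariance.
- Sample Size: "Considering a 20% potential attrition rate, 206 parent-child dyads in total are needed".

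Under Randomization, allocation follows baseline measurement. Any dyad withdrawing after allocation is therefore a randomised dyad with baseline records on file. The Results section reports data collection for 238 dyads and does not say how many were randomised, withdrew or were deleted.

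**The concern.** A likelihood-based mixed model is useful with dropout because a dyad seen at T2 but not at T3 still contributes its T2 value. The ethics rule erases that value when the dyad formally withdraws, so the two sections work against each other. Most analysis choices can be revised later. This one cannot, because no analysis plan or sensitivity analysis can recover deleted records.

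The stake is the comparison on the primary outcome, preschoolers' physical activity (PA). The arms ask very different things of parents. According to Intervention Procedure and Theoretical Foundation, eHealth parents get four push notifications and two self-monitoring messages a week, plus goal setting and private reminders if they do not post. Control parents get a weekly pamphlet. Reasons for withdrawing could therefore differ by arm. If less active families leave one arm more than the other, deletion makes the remaining arms less comparable. The baseline comparison would then cover non-withdrawers only, so it could not show the problem.

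**Working it through.** **1. The plan's own figure.** Taking the 82 dyads per arm from Sample Size as given, with 20% attrition: 82 / (1 − 0.20) = 102.5, rounded up to 103 per arm, 2 × 103 = 206. The stated total is reproduced.

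**2. How many dyads could be affected.** 206 × 0.20 = 41.2, so about 41, leaving about 165. This is a ceiling. It treats all attrition as formal withdrawal, and the article gives no withdrawal rate.

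**3. What deletion removes, by time of leaving.**

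- *Withdrawal before T2:* only T1 exists. The outcome occasions are T2 and T3, so the dyad has no outcome and the specified estimate is the same with or without its row. The loss is baseline data for describing the randomised sample, for imputation and for sensitivity analysis.
- *Withdrawal between T2 and T3:* T1 and T2 exist. The model would use T2 directly for the T2 contrast, and indirectly for T3 through the correlation between visits. Deletion removes both contributions.
- *Missed visit or invalid accelerometer wear without withdrawal:* the dyad stays in the file and the model handles it as planned.

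**4. Effect on the estimate.** This was simulated with 3000 runs and 103 dyads per arm. Assumptions, none from the documents: SD 1; correlation 0.5 between visits; true effect 0.30 SD at T2 and T3; all withdrawal between T2 and T3. Where withdrawal is outcome-related, it is likelier when T2 PA is low (a slope of 1.5 per SD with logistic noise). The analysis is adjusted for baseline. Data kept means the likelihood estimate using T2 values of withdrawers; data deleted means those dyads are gone.

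| Withdrawal, eHealth vs control | Kept: T2, T3 | Deleted: T2, T3 | SE at T2, kept to deleted |
|---|---|---|---|
| 30% vs 10%, purely random | 0.299, 0.295 | 0.301, 0.295 | 0.122 to 0.136 |
| 20% vs 20%, outcome-related alike in both arms | 0.301, 0.301 | 0.302, 0.301 | 0.121 to 0.133 |
| 30% vs 10%, outcome-related in both arms | 0.301, 0.295 | 0.463, 0.349 | 0.119 to 0.134 |
| 20% vs 20%, outcome-related in eHealth only | 0.299, 0.300 | 0.475, 0.358 | 0.119 to 0.133 |

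The first two rows show a loss of precision at T2 and no material bias. The last two show bias in favour of the intervention when its less active families leave selectively. Unequal rates alone do not cause bias, and equal rates with different reasons can.

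**5. Cross-check of the T3 figures.** With all correlations 0.5, the coefficient of T3 on T2 given baseline is (0.5 − 0.25) / (1 − 0.25) = 1/3. Selection on T2 should therefore pass one third of its bias to T3. Third row: (0.463 − 0.301) / 3 = 0.054, and 0.295 + 0.054 = 0.349, as simulated. Fourth row: (0.475 − 0.299) / 3 = 0.059, and 0.300 + 0.059 = 0.359, against 0.358 simulated.

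**The case against.** The case on the other side has real force.

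- *The rule covers withdrawal and the model covers missing measures; these overlap but are not the same.* This stands. A reader might infer that the analysis becomes completers-only and the mixed model is defeated. The article does not support that: dyads that miss a visit or fail the wear rule remain, and dyads leaving before T2 would have given this model no outcome anyway.
- *The direction of bias is not shown.* This also stands. Entry requires commitment to the full six months, parents are not told their allocation, and the reminders and peer contact are meant to support adherence. The article gives no withdrawal rates by arm. The biased scenarios above put all withdrawal between T2 and T3 and make it depend on outcome differently by arm, so they lean towards the unfavourable end.
- *The sentence is a commitment made to families under ethics approval.* This stands in part. Erasure on request is legitimate, and the consent form is not shown. As printed, however, deletion does not depend on a request.
- *Analysis sets may be defined in a fuller document, and CONSORT-EHEALTH reporting will give counts.* This does not answer the point. An analysis set cannot include records that have been deleted, and counts by arm do not replace outcomes.

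**Conclusion.** The contradiction is real: an unconditional deletion rule stands beside an analysis chosen for its use of partial records. The direct harm is confined to T2 outcomes of dyads that formally withdraw between T2 and T3. For earlier withdrawers the loss is baseline information. At most about 41 of 206 dyads are involved, and probably fewer, since not all attrition need be withdrawal.

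The cost in precision at T2 is modest: in the simulation, a standard error of about 0.12 rises to between 0.13 and 0.14. Bias is conditional. It needs withdrawal related to outcome in a way that differs by arm. Under the 30% vs 10% illustration, a true 0.30 SD reads as about 0.46 at T2 and 0.35 at T3.

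A reader might also put the harm at 0.20 × 0.5 SD = 0.10 SD, assuming that eHealth withdrawers average 0.5 SD below stayers. That figure measures selection from dropout as a whole. Part of it would remain if every record were kept, so it should not be charged to the deletion rule. Nor do the documents show that the effect will be exaggerated, only that it could be. The change is a cheap improvement well worth making; the material does not show that the trial's result is already compromised.

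**What to change.** Replace the deletion sentence with a rule that, on withdrawal, no further data are collected, and data collected up to then are kept in coded form and analysed in the randomised arm unless the parent asks for erasure. Report the numbers randomised, withdrawn and erased by arm.

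Recruitment, baseline and post-test collection are already finished, so new wording cannot by itself govern families who consented under a deletion promise. For them, keep data only with the ethics committee's agreement or renewed consent. Where records have already been deleted, state this as a limitation, with the counts by arm.

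The cost is a wording change, an ethics notification and possible re-contact of some families. Erasure on request is preserved.

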### Randomization

Once participants are recruited and baseline measurements are collected, participants will be randomly allocated to either an intervention group (eHealth group) or a control group (traditional group) in a 1:1 ratio through a computer-generated list, using the statistical software SPSS (IBM SPSS 27, IBM Corp). The randomization will be conducted by a researcher who is blinded to the intervention recruitment and delivery. Random allocation to either the eHealth group or the control group will not be informed to parents.

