### Primary Outcome

#### Preschoolers’ PA

The PA level and sedentary time will be objectively monitored using a triaxial accelerometer ActiGraph GT3X-BT (ActiGraph). The ActiGraph accelerometer has been found to be valid and reliable to objectively measure PA levels in preschoolers [72]. The kindergarten teachers and parents will receive written and video instructions for the use of the accelerometer. In addition, parents will be asked to register an activity diary for both wear and nonwear times. The accelerometer wear will be checked by teachers on each school day. An accelerometer will be affixed to the participant’s right wrist to monitor all activities for a period of 7 continuous days, except during periods of water-related activities or situations involving the risk of damage to the device, such as contact sports or self-defense. Data will be downloaded and initialized using the ActiLife software (version 6.13) and analyzed in 1-second epochs. Valid wear time will be considered at least 16 hours of wear time over at least 3 days (2 weekdays and 1 weekend day) [73]. Nonwear time will be defined by 60 consecutive minutes of 0 counts per minute (CPM), using ActiLife standard approaches. The accelerometer’s activity counts will be categorized into different intensities (ie, sedentary behavior, light PA, moderate PA, and vigorous PA) by using cutoff points as follows: sedentary, <819 CPM; light, 820-3907 CPM; moderate, 3908-6111 CPM; and vigorous, ≥6112 CPM.

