
This study has several strengths, including a randomized controlled trial design, calculation of sample size that ensures adequate statistical power, and objective and valid data collection methods for outcome measurements. Multiple lifestyle-related behaviors (ie, PA, diet, and sleep) are targeted in the intervention. The intervention delivery is grounded upon 4 behavioral modification steps included in SCT. A 3-month follow-up will determine whether the behavioral changes made during the intervention can be maintained. This study addresses many limitations summarized from previous studies, such as failure to either consider the imbalance of the intervention dose to bias the results or consider the sequence of the intervention contents to bias the results.

There are some limitations that need to be considered. The parent-child dyads that will be allocated to either the intervention or control group may be from the same school, and it is therefore possible that the intervention content may be contaminated. Thus, the outcome of this intervention may not be generalizable to preschoolers living in other cities in China. Owing to subjective measurements for the questionnaires, there is potential for parents to intentionally or unintentionally misreport; however, this is common in all free-living studies examining behavioral measures [96].

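### Certificates go to families judged more active and healthier, so the reward is tied to what the trial measures and could bias parent-reported secondary outcomes by arm

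*Protocol article*

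**What the plan says.** **Incentive.** Ethical Considerations states: "Incentives (honorary certificates) will be offered to families judged to be more active and healthier". It does not say who judges, on what information, when, whether both arms are eligible, or when families learn of it.

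**Outcomes.** Study Design states: "The primary outcome will be preschoolers’ PA". It continues: "The secondary outcomes will be preschoolers’ DB, preschoolers’ sleep duration and sleep problems, parents’ PA, parenting style, and parental feeding style". The Secondary Outcomes section also describes screen time and parents' self-efficacy, which are not in that list.

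**Blinding.** Study Design calls the trial a "2-arm, parallel, single-blinded, randomized controlled trial" without naming the blinded party. Randomization adds: "Random allocation to either the eHealth group or the control group will not be informed to parents".

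**Acknowledged limitation.** The Discussion concedes, for the questionnaires, that "there is potential for parents to intentionally or unintentionally misreport". It treats this as common to free-living studies and does not mention the certificates.

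**The concern.** A reward for attending and completing assessments helps retention and leaves the answers alone. A reward for being active and healthy gives families a reason to appear so. Where the outcome is a parent's own rating, that can shift the answers; where it is a device worn for one week, it can shift that week's behaviour.

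A shift shared by both arms does little harm to the comparison. What matters is a shift that differs by arm, because the trial could not then separate it from an intervention effect. An unexplained single-blind label may also lead readers to credit the parent-reported outcomes with a protection they probably lack.

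**Working it through.** The plan gives no figure for this point, so the check sets the sections side by side.

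**1. Is the reward tied to the outcomes?** The criterion has two parts, more active and healthier. Child physical activity is the primary outcome; parents' physical activity, eating behaviour and sleep are secondary. The overlap is direct, and no section separates the award from the outcome data.

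**2. Which outcomes rest on parents' answers?**
- Study Design names six secondary outcomes. Five are parent questionnaires: eating behaviour, sleep problems, parents' physical activity, parenting style and feeding style. The sixth, sleep duration, is accelerometer-based but matched with a parent log.
- The Secondary Outcomes section adds two more parent questionnaires, screen time and self-efficacy, giving 5 + 2 = 7 of 6 + 2 = 8 measures described.
- Those closest to the certificate's wording are eating behaviour, sleep problems, parents' physical activity and, if analysed, screen time. Nothing shows that the certificate rewards a parenting style, a feeding style or self-efficacy.

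**3. Can parents tell their arm?** Intervention Procedure gives one arm a WeChat group, a kindergarten teacher as captain, videos, weekly goals and feedback. Control Group gives the other a weekly pamphlet carried home by the child. The Discussion says both arms may share a school. Withholding the allocation does not hide so visible a difference. That parents recognise their arm is an inference, but a strong one.

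**4. Could the effect differ by arm?** For a parent-reported outcome, let b be the mean reporting shift in each arm:

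observed difference = true difference + (b_intervention − b_control)

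- If the shifts are equal, the bracket is zero and the bias cancels.
- One route to unequal shifts is visibility. Intervention parents answer two self-monitoring messages a week and are encouraged to share goal achievements with the group or facilitator. No such channel is described for control parents.
- Randomization places baseline measurement before allocation. A shift that depends on arm can therefore arise only afterwards, and baseline adjustment would not remove it.

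**5. Does it reach the primary outcome?** Child activity is recorded by an ActiGraph over seven days, with wear checked by teachers on school days. Questionnaire misreporting cannot alter the counts. What remains is unusual activity or wear during that week. Parents do have a part in the record, since "parents will be asked to register an activity diary for both wear and nonwear times", but the article defines nonwear from runs of zero counts.

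**The case against.** The strongest reply is that a between-arm bias is not shown. The article does not restrict certificates to one arm, say that outcome data decide them, or say that families knew beforehand. The recruitment section mentions explaining benefits that parents receive after the study but does not connect this to certificates. A reward offered alike to everyone could leave the comparison almost untouched. This stands, and it limits the point to a plausible and avoidable risk.

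Second, possible misreporting is already declared as a limitation. That deserves credit, but the declaration treats it as a general feature of such studies, whereas the certificate rule is a choice made by this trial.

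Three stronger readings are tempting, and the document does not support them:

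- **That the main result is exposed to misreporting.** It is not, because the primary outcome is measured by device.
- **That only the intervention arm knows the target behaviours.** Both arms receive recommendations on activity, diet and sleep. The arms differ in individual goals, feedback and interaction.
- **That the bias can be sized.** A reader might assume a differential shift of 0.1 to 0.2 SD and set it against the planned d of 0.3 (0.1/0.3 = 33%; 0.2/0.3 = 67%). Nothing in the article anchors that range, so the ratios are no estimate of the bias.

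**Conclusion.** The concern holds in limited form. The stated criterion rewards the constructs the trial measures, and withholding the allocation probably does not blind parents. Together these create an avoidable risk of arm-dependent reporting in eating behaviour, sleep problems, parents' physical activity and, if analysed, screen time. The primary outcome is exposed only through behaviour or wear in the measured week.

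Neither size nor direction can be estimated from the document. The conclusion assumes that families knew of the criterion before an assessment, that parents recognise their arm, and that the incentive acts unequally across arms. If any of these fails, the between-arm bias shrinks or disappears.

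The blinding label is a related but separate matter. The article blinds the person who randomises to recruitment and delivery, and the facilitators to the study objectives. Neither amounts to blinding parents or analysts to arm.

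**What to change.** - **Any assessment still to be done:** award the same certificate in both arms for completed assessments (valid accelerometer wear and all questionnaires), not for activity or health level. The certificates stay the same and only the criterion changes. The small cost is a possible notification to the ethics committee.
- **If certificates were already awarded on the stated criterion:** report who judged, on what data, when parents were told, and how many were awarded in each arm. This may be all that is left to do. The Results section places follow-up in June 2024 as still to come, yet reports completed data collection for 238 dyads with analysis under way.
- **Blinding:** state who was actually blinded under the single-blind label. Do not claim analyst blinding unless it was done; no section describes it.
- **Interpretation:** treat the parent-reported outcomes as unblinded, and name the certificate rule beside the misreporting limitation in the Discussion.

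The last three items need only a few sentences of reporting and a count from the award records.
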